### Objectives

We propose to generate preliminary data on high-risk groups’ health beliefs, barriers, and intent to receive the influenza vaccine. We will also generate preliminary data on the acceptability, cost-effectiveness, and required capacity for facility-based influenza vaccination for informing policy decisions regarding influenza vaccination among the high-risk population in Bangladesh.

## Methods

This study will employ a quasi-experimental design that aligns with the STROBE guidelines. Additionally, this design will incorporate sensitivity analyses to explore the impact of uncertainty in parameter estimation precision on the outcomes of deterministic Markov decision-analytic models.

### Study design

We will conduct our study leveraging the ongoing HBIS platform, a network of nine tertiary-level hospitals across Bangladesh [19, 25]. The structure and operational aspects of the HBIS platform have been previously discussed [19, 25]. Our study design will be quasi-experimental. To meet the vaccine acceptability objective, we will collect data on participants’ health beliefs, barriers, and vaccination intentions using the health belief model (HBM) from patients meeting criteria for high-risk populations attending two public tertiary-level hospitals. To meet the influenza vaccination cost-effectiveness objective, in one of the two hospitals, we will conduct an influenza vaccination campaign before the influenza season, where the vaccine will be offered free of cost to high-risk patients, and in the second hospital, vaccination will not be offered. Both the vaccinated and unvaccinated participants will then be followed-up once a month for one year to record any influenza-like illness, hospitalization, and death. Additional data for vaccination cost-effectiveness objectives on direct and indirect costs associated with influenza illness will be collected from ILI and SARI patients at one public and one private hospital. To meet the required capacity for a facility-based influenza vaccination objective, we will collect secondary data, including the Statistical Yearbook of Bangladesh 2020, as represented in Table 1 [26–28].

**Table 1 Tab1:** Assumptions and data sources by each target group

Target Group	Assumption and data sources
Children 6 months to 8 years, influenza vaccine doses	Two doses will be delivered, each four weeks apart [31, 32]. Data of the total number of < 5 years children will be adopted from the Statistical Yearbook of Bangladesh 2020 [26]. Monthly the number of children < 8 years visited hospitals will be collected from respected hospitals or respective District Civil Surgeon Office [29, 30, 33].
Pregnant women’s influenza vaccine doses	One dose to all pregnant women (any trimesters). The crude birth rate is assumed to be 21.9% (BDHS 2017-18) [34]. Influenza vaccines were distributed evenly across the childbearing years 15 through 49 [34]. Data on the total number of women of childbearing age (15–49 years) will be collected from the Statistical Yearbook of Bangladesh 2020 [26]. Monthly pregnant women who visited hospitals will be collected from respective hospitals or respective District Civil Surgeon Office [29, 30, 33].
Elderly ≥ 60 years influenza vaccine doses	One dose for all persons aged 60 years and older. Population data from the Statistical Yearbook of Bangladesh 2020 [26]. Monthly the total number of ≥ 60 years aged patients visited hospitals will be collected from respected hospitals or respective District Civil Surgeon Office [29, 30, 33].
Adults with chronic diseases, influenza vaccine doses	One dose for all persons with chronic disease. We will use the prevalence of having any chronic illness from the Bangladesh Household Income and Expenditure Survey (HIES) 2010 [35]. Then, the total number of persons with any chronic illness will be estimated using data from the Statistical Yearbook of Bangladesh 2020 [26]. Monthly patients with chronic diseases visited hospitals will be collected from respected hospitals or respective District Civil Surgeon Office [29, 30, 33].

We will conduct all the study activities through close collaboration with the Institute of Epidemiology Disease Control and Research (IEDCR) of the Ministry of Health and Family Welfare (MoH&FW), the Government of Bangladesh. We will also collaborate closely with the administration of the participating hospitals, especially the hospital director, to guarantee the hospitals’ participation, support, and cooperation. We will work with the line director and directors of study hospitals to implement the vaccination. We will utilize hospital resources and leverage existing staff to vaccinate study participants. Figure 1 illustrates the study activities and data collection flow chart.

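### Table 1 fixes two wrong population inputs for the dose and cold-chain estimate: a crude birth rate in percent beside a count of women aged 15–49, and an under-5 count for a target of 6 months to 8 years

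*Protocol article*

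**What the plan says.** Table 1, under Study design, lists the assumptions and data sources for each target group.

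- **Pregnant women.** The dose rule is "One dose to all pregnant women (any trimesters". The rate is given as "The crude birth rate is assumed to be 21.9% (BDHS 2017-18". The population source is "Data on the total number of women of childbearing age (15–49 years) will be collected from the Statistical Yearbook of Bangladesh 2020". The row also says that vaccines are spread evenly over the ages 15 to 49.
- **Children.** The row is headed "Children 6 months to 8 years, influenza vaccine doses" and gives two doses per child. The population source is "Data of the total number of < 5 years children will be adopted from the Statistical Yearbook of Bangladesh 2020". The hospital count in the same cell uses another age limit: "Monthly the number of children < 8 years visited hospitals will be collected".
- **Elderly.** "One dose for all persons aged 60 years and older".
- **Adults with chronic diseases.** "One dose for all persons with chronic disease". The number is to come from the prevalence of any chronic illness in a 2010 household survey, combined with yearbook data. The row's text gives no age limit and no population base, although its heading says adults.

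The section on data sources for required capacity points to Table 1 for the size of each risk group in the catchment area. The matching analysis section turns these sizes into annual doses, injection equipment and storage volume, and compares the volume with each hospital's cold storage. The section on disease-burden data sources also cites Table 1.

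**The concern.** The capacity objective is a chain of multiplications: people in the group, doses per person, volume per dose. An error in the first factor passes in full to doses, syringes, safety boxes and litres of cold storage. Two of the four rows have a wrong first factor as printed: one has an impossible unit and a denominator that does not belong to it, the other an age band that does not match its target. The two rows need not err in the same direction, so they cannot be assumed to cancel.

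This is not detail left for a later document. The article states these inputs itself, and an analyst who followed Table 1 would carry the errors forward.

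**Working it through.** The plan prints no dose count or storage volume derived from Table 1, so there is no result to reproduce. The check is on the inputs.

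**(a) Birth rate.** Inputs from Table 1: 21.9%, women aged 15–49, one dose per pregnant woman. The share of women aged 15–49 in the population is not given; I assume 25–29%.

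Plausibility of the percent sign: if yearly births were 21.9% of the total population, the fraction of women 15–49 delivering each year would be 21.9/29 = 76% to 21.9/25 = 88%. That is impossible. At 21.9 per 1,000 it would be 7.6% to 8.8%.

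Table 1 does not say how rate and count are combined. Per 100,000 catchment population, taking 21.9 births per 1,000 total population (2,190 births) as the reference:

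| Reading | Count | Ratio to 2,190 |
|---|---|---|
| 21.9% of total population | 21,900 | 10 |
| 21.9% of women 15–49 | 0.219 × 25,000 to 29,000 = 5,475 to 6,351 | 2.5 to 2.9 |
| 21.9 per 1,000 women 15–49 | 0.0219 × 25,000 to 29,000 = 548 to 635 | 0.25 to 0.29 |

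Widening the assumed share to 22–30% changes the last two ratios to 2.2–3.0 and 0.22–0.30. The third line shows that correcting the unit alone, and leaving the denominator, would give about a quarter of the births.

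The second line is not impossible in itself. It equals 0.219 × 35 = 7.7 births per woman over the 35 childbearing years, but it is then no longer a crude birth rate.

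**(b) Children.** Inputs from Table 1: target 6 months to 8 years, two doses, population count under 5. Assume equal yearly cohorts of n children.

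- Doses from the under-5 count: 2 × 5n = 10n.
- Target up to the 8th birthday: 2 × 7.5n = 15n. Shortfall 1 − 10/15 = 33%.
- Target through age 8: 2 × 8.5n = 17n. Shortfall 1 − 10/17 = 41%.

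The under-5 count also includes infants below 6 months, who are outside the target. Without them it covers 4.5/7.5 = 60% or 4.5/8.5 = 53% of the target span. The under-8 limit for hospital visits is a third band; it too includes the youngest infants, and it omits 8-year-olds if they belong to the target.

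**(c) Overlap.** A person aged 60 or over with a chronic illness meets two row definitions, as does a pregnant woman with one. If the elderly and chronic-disease rows are added, the excess is overlap ÷ (elderly + chronic − overlap). None of the three quantities is in the document. Assuming elderly 6–10% of the population, chronic illness 10–20%, and 30–70% of the elderly chronically ill, the excess runs from 7% to 54%. A range that wide only shows that the size cannot be derived here.

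**The case against.** The best reply is that Table 1 lists sources, not formulas, and that a condensed article may leave the formulas to the full protocol. On that view the percent sign is a slip, and the even spread over ages 15 to 49 may only mean that births are distributed over maternal ages. The under-5 figure may be extrapolated later, and each row also has a hospital-visit count. Objective 3 is a desk calculation on secondary data that enters neither enrolment, the sample sizes nor the effectiveness analysis, so it can be corrected at analysis.

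Much of this stands, and it limits the point. A reader might infer from the table above that the pregnant-women count will be wrong by a particular factor. The document does not support that, because it states no multiplication. A reader might also infer that people with chronic illness who are elderly or pregnant will be counted twice. The text names no whole-population base and no summing rule. The abstract's promise of a total storage volume suggests a sum but does not exclude de-duplication.

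What the reply does not remove is that the unit is wrong by definition, that the only population count listed with the rate is not its denominator, and that the child population count does not cover the stated target. The under-8 figure counts hospital visits and does not repair the population base.

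**Conclusion.** Parts (a) and (b) hold and should be corrected before the capacity estimate is run.

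- **(a)** The unit error follows from the definition of a crude birth rate and the arithmetic above, without the cited survey. The effect on the dose count is undetermined in size and direction: several-fold too high or too low, depending on an unstated combination and on the assumed share of women 15–49.
- **(b)** Child doses are understated by about 33–41%, if the under-5 count is used unadjusted and yearly cohorts are equal.
- **(c)** This is a lesser point: overlap between rows is not addressed, and its size cannot be derived.

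Two stronger conclusions are tempting. One is that the feasibility judgement will be wrong. This cannot be shown, because the document gives neither the required volume nor the cold-storage capacity, hence no margin. The other is that the cost-effectiveness results are compromised through the second citation of Table 1. The ratios are calculated within each risk group, so group size largely cancels apart from fixed costs, and the effect is likely small.

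**What to change.** In Table 1:

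1. Check the rate against the cited survey, then state it per 1,000 and apply it to total catchment population. Alternatively, use a general fertility rate with the count of women aged 15–49. Change unit and denominator together, and write out the formula.
2. Replace the under-5 source by a population count for 6 months to 8 years, interpolated from published age bands if needed. Say whether 8-year-olds are included, and align the age band of the hospital-visit records with it.
3. State whether the rows are summed for the total storage volume. If so, subtract the overlap of the chronic-disease row with the elderly and pregnant rows, using age-specific prevalence where available. Applying an all-age prevalence to adults under 60 would bring a bias of its own, because chronic illness may vary with age.

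The cost is new wording in Table 1, a spreadsheet change and possibly some interpolation. No new participant data are needed.

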**Fig. 1 Fig1:**
[figure not shown]
Flow chart showing different elements of study activity and data collection

### Study setting

We selected study hospitals considering several factors. Firstly, we will use the hospital-based influenza surveillance (HBIS) platform to conduct this study. We have chosen Rajshahi Medical College Hospital and Khulna Medical College Hospital for our study activities on high-risk groups’ vaccine acceptability and cost-effectiveness. We will enroll Severe acute respiratory illness (SARI) and influenza like illness (ILI) patients identified from the HBIS platform to meet our study objectives. We will also collect influenza virus test results from the HBIS platform and data on influenza illness episodes’ costs from the influenza-positive SARI and ILI patients. This approach will save influenza virus testing costs not allocated in the current study budget. Secondly, to assess the outcome of influenza vaccination, we plan to enroll patients from public tertiary-level hospitals (one treatment/vaccinated and the other control hospital) to minimize baseline differences between the treatment/vaccinated and control arm. Thirdly, we have chosen Ragib-Rabeya Medical College & Hospital to represent public and private healthcare facility cost differences while estimating the costs of influenza illness. A brief description of the study sites’ bed occupancy rate and average monthly admission are represented in Table 2 [29, 30].

**Table 2 Tab2:** Demographic characteristics of the study hospitals

Study sites	Bed occupancy rate (%)	Total no OPD visits	Total number of PNC visits	Total number of admission	Middle wealth quantile
Rajshahi Medical College Hospital	198.05	114,818	2,405	22,022	24.1%
Khulna Medical College Hospital	275.00	35,311	991	8,859	24.8%
Jalalabad Ragib-Rabeya Medical College & Hospital	NA	NA	NA	NA	15.8%

Source: Local health bulletin October 2022

OPD = outpatients care department; PNC = post-natal visit

Note: a bed occupancy rate greater than 100% indicates that these hospitals receive and care for more patients than their capacity

Study sites for influenza vaccine acceptability, health beliefs, barriers:

We will conduct a health belief model (HBM) survey in two conveniently selected hospitals:

Rajshahi Medical College Hospital, Rajshahi.Khulna Medical College Hospital, Khulna.

Study sites for influenza vaccination cost-effectiveness objective:

For this specific objective, we will collect data on the health outcome of vaccination and the cost associated with influenza illness. Data on health outcomes will be collected from two public tertiary-level hospitals. The cost associated with influenza illness data will be collected from one public and one private hospital. Figure 2 represents the study sites.

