### Data collection to determine vaccination cost-effectiveness

#### Vaccination campaign

To record health outcomes after influenza vaccination, in one of the two public tertiary-level study hospitals, we will conduct an influenza vaccination campaign before the influenza season, where the vaccine will be offered free of cost to high-risk patients, and in the second hospital, vaccination will not be offered. We will work with the hospital administration to set up a vaccination booth on the hospital premises. Vaccines will be made available at the vaccination booths. Posters and leaflets containing information on influenza vaccination will be displayed at the vaccination booths and key hospital locations with information on the vaccination. Inpatients and outpatients of all departments will be informed about the ongoing immunization campaign. Eligible patients will be offered to take the vaccine during the vaccination campaign. Benefits, significance, adverse effects, and how to manage them will be explained to the patients. Nurses/ Health Assistants (HA) will provide influenza vaccination throughout the campaigns. At 8 AM, the vaccination booth will open and close at 2 PM, six days a week throughout the campaign period. A vaccination card will be issued to the participants. All high-risk groups will get one dose of seasonal influenza vaccination (Quadrivalent), except children aged six months to 8 years, who will receive two doses four weeks apart [31, 32]. All vaccines will be the southern hemisphere vaccine as recommended by the WHO for Bangladesh. Regarding children, we will make phone follow-ups with the guardians of the children receiving the first dose to remind them about the second dose schedule, and it will be recorded in the vaccine card if the second dose is received. In order to ensure the availability and quality control of vaccines throughout the three-month campaign period, the research team at icddr,b will closely monitor the campaign. All vaccinated participants will receive notification regarding potential adverse events following immunization (AEFI) during the vaccination process. To document any untoward occurrences after Adverse Events Following Immunization (AEFI), we will adhere to the pre-existing surveillance mechanism implemented by the World Health Organization (WHO) and the Ministry of Health and Family Welfare (MoHFW) of the government of Bangladesh. During the vaccination campaign briefing session in each study hospital, participants will be informed about the process of reporting any Adverse Events Following Immunization (AEFI) within the hospital’s established surveillance system. Additionally, participants will be provided with the mobile number, as stated in the consent form, to report any such issues. Furthermore, during the vaccination campaign implementation, a representative from icddr,b will be assigned to each study hospital to oversee and monitor any adverse events following immunization (AEFI) in conjunction with the hospital’s existing surveillance system. If an Adverse Event Following Immunization (AEFI) case is identified, the personnel affiliated with icddr,b will promptly notify the Hospital Surveillance Officer (HSO), provide support to the HSO in completing the AEFI report form, and subsequently transmit it to the Expanded Programme on Immunization (EPI) headquarters via the Chief Health Officer.

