
In the second hospital, we will enroll participants meeting the high-risk group individual criteria. However, no vaccination campaign will be conducted. We will name this group as an unvaccinated cohort.

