## Study size

### Sample size and sampling

#### The sample size for the vaccine acceptability objective

Our study design will be quasi-experimental. Our primary outcome for vaccine acceptability is the intention to receive the influenza vaccine. Based on studies utilizing the high-risk group-specific health belief model conducted in neighboring countries, it has been found that 91% of elderly people, 88% of adults with chronic illness, 76.3% of pregnant women, and 62.4% of parents with six to three-year-olds expressed their intention to get the influenza vaccine [38–40, 45]. We expect a similar positive intention to receive the influenza vaccine, ranging from 62 to 91% for our target study population. In this study, we employed a significance level of 5%, a power of 80%, a design effect of 1.2, and account for a non-response rate of 10% to determine the required sample size [65–67]. We will utilize a validated health belief model tool. To avoid selection bias, we will use random assignment to the study based on predefined inclusion and exclusion criteria. We will also provide training to study staff about random enrolment of the study participants based on inclusion and exclusion criteria. Table 5 represents the estimated sample size by the high-risk group for the vaccine acceptability objective.

**Table 5 Tab5:** Estimated sample size for investigating the vaccine acceptability/ intention to receive, health outcome due to vaccination, and cost-effectiveness of implementing a facility-based influenza vaccination

High-risk group	The sample size for the vaccine acceptability survey	The sample size for vaccine effectiveness	The sample size for the cost-components survey
Children 6 months to 8 years	659	465	60
Pregnant women	495	756	39
Elderly ≥ 60 years	330	736	56
Adults with chronic diseases	425	610	31

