#### The sample size for the vaccine effectiveness objective

Our primary outcome for health outcome for vaccination is vaccine efficacy against influenza among high-risk group populations. Studies from neighboring countries found that ILI symptoms were 15.30% of children, 31.23% of adults with chronic illness, 10.97% of pregnant women, and 20% of the elderly [68–70]. A systematic review of seasonal influenza vaccine policy, use, and effectiveness also revealed that pooled vaccine effectiveness for high-risk groups in the tropics and subtropics ranged from 48 to 88% (10). We expect a similar vaccine efficacy between 50 and 81% for our study’s targeted high-risk group population. A 5% significance level, 80% power, design effect 1.2, and 10% non-response were used to calculate the required sample size to estimate vaccine effectiveness [65–67]. Table 5 represents the high-risk group’s estimated sample size for vaccine effectiveness.

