### Data analysis for cost-effectiveness analysis

#### Vaccine efficacy estimation

We will utilize Poisson regression to calculate the rate ratios (RRs) of participants who will receive influenza vaccination compared to those who will not. In the final model, we will include all the variables that will incorporate all variables that exhibit a confounding effect or demonstrate statistical significance at a significance level of 5%. The investigation of additional potential effect modifiers will be conducted by incorporating interaction terms. We will calculate vaccine effectiveness with 95% CI for each risk group ( (1 - RR) * 100) [72].

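### Vaccine effectiveness is fully confounded with hospital, and its 95% CI leaves out between-hospital variation

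*Protocol article*

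**What the plan says.** All references are to the protocol article.

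- **Allocation.** One of two public tertiary hospitals runs a free vaccination campaign; "in the second hospital, vaccination will not be offered" (Vaccination campaign). High-risk patients enrolled there form the comparator: "We will name this group as an unvaccinated cohort". The text does not say which of the two hospitals vaccinates.
- **Sites.** "Data on health outcomes will be collected from two public tertiary-level hospitals" (Study setting). For the health belief survey, the same pair is described as "two conveniently selected hospitals".
- **Justification.** Both arms come from public tertiary hospitals, "one treatment/vaccinated and the other control hospital) to minimize baseline differences between the treatment/vaccinated and control arm" (Study setting).
- **Analysis.** Poisson regression compares vaccinated with unvaccinated, and VE is one minus the rate ratio, with a 95% CI for each risk group (Vaccine efficacy estimation). Covariates stay in the model if they show a confounding effect or "demonstrate statistical significance at a significance level of 5" percent.
- **Limitation.** The Discussion acknowledges the small number of facilities, but only as a limit on generalisability.

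**The concern.** Every vaccinated participant comes from one city and every control from another. Differences between the cities in influenza activity, care seeking or the reporting of illness by phone will appear in the rate ratio as vaccine effect. A second selection adds to this: the vaccinated are people who took up an offer, whereas the controls mix would-be acceptors with would-be refusers.

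VE is the named primary health outcome and the first step of the cost-effectiveness analysis, whose results are meant to inform national policy. A biased VE with too narrow an interval would pass into the cases averted and the ICER unseen.

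**Working it through.** **1. Identifiability.** The sections Vaccination campaign and Vaccine efficacy estimation together make exposure = hospital. Two hospitals less two arm means leaves 2 − 2 = 0 degrees of freedom for between-hospital variance. A hospital term would be collinear with vaccination. Patient-level covariates can reduce measured patient-level imbalance, but cannot remove hospital-level differences.

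**2. Bias from a site difference.** Apparent VE = 1 − (1 − true VE) × site rate ratio. The site ratios are assumptions.

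| Site rate ratio | True VE 0% | True VE 50% |
|---|---|---|
| 0.8 | 20% | 60% |
| 1.0 | 0% | 50% |
| 1.25 | −25% | 37.5% |

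The error does not shrink as the sample grows.

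**3. False-positive rate of the nominal 5% test.** Inputs: illness proportions p from the VE sample-size section; N from Table 5, read as totals (the table does not say whether they are totals or per arm); 10% loss, so n = 0.9N/2 per hospital. The between-hospital CV is an assumption, since the documents give none.

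- Sampling SE of the log ratio, illness treated as yes/no: se = √(2(1 − p)/(pn)).
- SE used by the test: s = se × √1.2. This is generous, because nothing in the analysis section says the design effect is applied to the CI.
- True SD: √(se² + 2 ln(1 + CV²)).
- Rejection rate under no effect: 2 × (1 − Φ(1.96 s / true SD)).

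Children at CV 20%: n = 0.9 × 465/2 = 209.25; se = √(1.694/32.0) = 0.230; s = 0.252; true SD = √(0.0529 + 0.0784) = 0.362; 1.96 × 0.252/0.362 = 1.36, giving 17%.

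| Group | N | p | se | CV 10% | CV 20% |
|---|---|---|---|---|---|
| Children | 465 | 0.1530 | 0.230 | 7% | 17% |
| Pregnant women | 756 | 0.1097 | 0.218 | 7% | 19% |
| Elderly | 736 | 0.20 | 0.155 | 11% | 30% |
| Chronic disease | 610 | 0.3123 | 0.127 | 15% | 38% |

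Without the √1.2 the ranges are 9–19% and 21–42%. With Table 5 read as per-arm sizes (n = 0.9N) and √1.2 kept, they are 10–25% and 28–51%.

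**4. Floor on precision.** At CV 20% the site component alone contributes √(2 ln 1.04) = 0.28 to the SE. At VE 50%, even with unlimited participants, the interval would be 1 − 0.5 × exp(±1.96 × 0.28), about 13% to 71%.

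**5. Could off-season illness act as a built-in control?** A hospital × season contrast has variance equal to the sum of reciprocals of the four expected counts: 1/(npf) + 1/(0.5npf) + 2/(np(1 − f)), with f the share of illness in season and VE 50%. For children at f = 0.5, npf = 16.0; variance = 0.0625 + 0.125 + 0.125 = 0.312; SE = 0.559; z = 0.693/0.559 = 1.24, so power is about 24%. For f from 0.5 to 0.7 (assumption) power is 22–24% (children), 25–27% (pregnant women), 40–43% (elderly) and 49–53% (chronic disease).

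**The case against.** The article is open about being quasi-experimental and preliminary. In context, the baseline sentence most naturally says that taking both arms from public tertiary hospitals makes them more alike. That is sensible restriction, and in Table 2 the share in the middle wealth group is nearly equal (24.1% and 24.8%). This stands as far as it goes. Restricting hospital type does not minimise differences between two cities, and the article never names site confounding.

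Several stronger readings are tempting but unsupported:

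- **That the protocol claims random allocation of vaccine.** "To avoid selection bias, we will use random assignment to the study" is in the acceptability sample-size section and concerns enrolment. It is not a claim about the VE comparison.
- **That the design effect was meant to cover hospital allocation.** "A 5% significance level, 80% power, design effect 1.2, and 10% non-response were used" is a generic allowance, repeated for the acceptability and cost samples. It enlarges N; the article does not say it handles one hospital per arm, so it is not part of this error.
- **That Table 2 shows different patient risk.** Outpatient visits (114,818 v 35,311), admissions (22,022 v 8,859) and bed occupancy (198% v 275%) measure hospital volume and load, not patients' risk of illness.
- **That covariates are chosen on significance alone.** The rule also keeps variables with a confounding effect.
- **That the bias has a known direction.** Nothing in the documents gives its sign or size.

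An article may leave a covariate list to a fuller plan. Here, however, it states a data-driven rule, and that rule is what should change.

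**Conclusion.** The point holds. As designed, VE cannot be separated from hospital, and the planned 95% CI excludes hospital-level variation. The claim that the layout minimises baseline differences should not stand, and the limitations miss the main threat to validity.

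The structural conclusion needs no assumption. The sizes do: false-positive rates of about 7–38% rest on a between-hospital CV of 10–20% and Table 5 read as totals, and the spurious VE of 20% rests on a site rate ratio of 0.8. They illustrate scale and are not estimates for these two hospitals. No analysis of the planned data fully removes the problem; it can be reduced, bounded and stated.

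**What to change.** 1. **Vaccine efficacy estimation.** Replace selection by observed confounding or p < 0.05 with a fixed list of covariates the study records, for example age, sex, income, comorbidity, inpatient or outpatient status, and symptoms in the previous 30 days.
2. **Key sensitivity analysis.** Compare vaccinees with control-hospital participants who stated an intention to be vaccinated, among those with survey data. This addresses acceptors versus non-acceptors, not site. It will cover part of the cohort only: in three of the four groups Table 5 gives a smaller survey sample than VE sample.
3. **Study setting and Discussion.** Withdraw the baseline claim; state that VE is confounded with site and that the CI excludes hospital-level variation.
4. **Cost-effectiveness estimation.** Carry a range of site rate ratios, for example 0.8 to 1.25, into the VE input of the PSA by dividing the observed rate ratio by the site ratio.
5. **Optional and exploratory only.** A hospital × season contrast. It removes only time-stable site differences, so local influenza activity in season stays confounded, and its power is about 22–53% at VE 50%. It also needs off-season data. The follow-up section covers the influenza season, whereas the Abstract, Study design and Discussion give one year; these must be reconciled first.

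The cost is analysis wording, a few lines of code, somewhat wider VE and ICER intervals, and less favourable wording. No new sites or participants are needed.
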